**QoL**^d^**, health-related**								
	Heart-QoL				✓			✓
	EQ-5D-5L^e^				✓			✓
**Medication adherence**								
	Self-reported				✓			✓
	Pharmacy refill							✓
Hospital admissions								✓

^a^Sent after the physician visit.

^b^EHR: electronic health record.

^c^BMQ-S: Beliefs about Medicines Questionnaire-Specific.

^d^QoL: quality of life.

^e^EQ-5D-5L: EuroQoL questionnaire [31,32].

Another registry, the national “Öppna Jämförelser” (Open Comparisons), measures the proportion of patients who have had a myocardial infarction and who fill a prescription for a statin 12-16 months later. The report from 2012 stated that 80% of myocardial infarction patients from Kalmar County Hospital filled a statin prescription [34]. To detect a difference of 10% in the proportion of patients with refill adherence, with 80% power at a significance level of *P*=.05 (two-sided), 195 patients would be required in each group.

We assumed an attrition rate of 40% in the intervention group and 60% in the control group, because the protocol for the latter can be regarded as an extended questionnaire study. Because patients were enrolled about 2 months before they were asked to fill in the first set of questionnaires, we assumed a high attrition rate at this stage, and because they are volunteers, we wanted withdrawal from the study at this stage to be a simple process. Patients who did not answer these first questionnaires will not be included in the outcome analyses.

On the basis of our primary outcome (LDL-C goal achievement) and expected attrition rate, a sample size of 130+140 patients (intervention plus control) would be required. However, this would not have the power to detect a meaningful difference in adherence (one of the secondary outcomes). As one of the problems encountered in prior intervention studies has been the lack of power to detect differences in both adherence and clinical outcomes, we based our sample size calculation on the number required to show a difference in adherence, that is, 195 patients at follow-up.

We therefore aimed to include 273+312 (=585) patients in the intervention and control groups, with an allocation ratio of 1:1.14.

#### Amended Sample Size Calculation in 2016

During the study, we learned two things that greatly impacted our sample size: (1) the goal achievement in standard care improved significantly and (2) our assumed attrition rate was too high. As described earlier, problems with recruitment also delayed the study, and this was another incentive to look at the required sample size.

The goal achievement for LDL-C in 2012 did not reflect the circumstances during our follow up in 2014-2017 because treatment possibilities changed the likelihood of reaching the target (the atorvastatin patent expired in 2013 and local guidelines successively changed, based on this). In 2015, the proportion of patients reaching the target was 0.5 nationally and 0.45 at Kalmar Hospital [35]. This reduced the power of the study to reject the null hypothesis unless the sample size was increased. On the other hand, our estimated attrition rate of 40-60% was shown to be too high, as only 16.9% (71/418) patients failed to return their baseline questionnaires, and with exclusions for other reasons (after obtaining patient consent), our attrition rate was 23% up to baseline assessment. We calculate the attrition based on this because all patients who filled in the baseline questionnaires, who do not later contact us to withdraw their consent, can be assessed for the primary outcome (LDL-C) as well as the pharmacy fill adherence and hospital admission outcomes, even if they drop off and fail to return follow-up questionnaires. As the assumptions behind the sample size calculation for the adherence measure are very uncertain and our funding would not permit recruitment after the end of 2016, we prioritized power for the primary outcome, and it was decided to end recruitment when at least 400 patients had consented or in December 2016 at the latest. The new calculation was based on the goal achievement of 0.45 at Kalmar Hospital and our expectation to reach 0.6 in the intervention group. This would mean 170 patients needed in each group for a power of 80% to reject the null hypothesis, or 134 needed for 70% power.

### Outcomes

#### Primary Outcome

The primary outcome parameter of the MIMeRiC trial is the proportion of patients who reach the treatment goal for LDL-C levels. The treatment goal, as assessed by SEPHIA, is an LDL-C of <1.8 mmol/L, or a reduction of 50% from baseline.

LDL-C was chosen as the primary outcome because it is an objective measure of a variable related to the risk of recurrent disease. The national quality registry data indicate that it is more difficult to reach treatment goals for LDL-C than for systolic blood pressure [33], and we also regarded the measurement of LDL-C at a single laboratory to be more reliable than blood pressure measurements at several different health care facilities.

The assessment of LDL-C is part of the follow-up process in SEPHIA, and the test is administered by the cardiology outpatient clinic for all patients with acute myocardial infarction. Patients with other forms of CHD will be followed by the research team for this assessment and asked to go to their primary care facility or the cardiology outpatient clinic for assessment, whichever is most convenient for them. LDL-C values are calculated from the serum concentrations of cholesterol and fasting triglycerides, using the Friedewald formula.

#### Secondary Outcomes

##### Patient Adherence

The proportion of patients who adhere to the treatment regimen will be assessed using self-reporting and refill data. The phases of adherence under study are implementation and persistence, as defined by the ABC-taxonomy [36]. Because self-reporting and refill data have their individual disadvantages, they will be combined [37]; thus, the patient is considered nonadherent if either they are nonpersistent according to refill data or they are nonadherent according to self-report. However, as self-reporting is only possible for one medication per questionnaire [38], we will use this combined measure only for cholesterol-lowering drugs, as they relate to our primary outcome.

Self-reported adherence to cholesterol-lowering drug regimens will be measured with the MMAS-8 [38-40]. Although this has been validated in hypertension, studies have validated the earlier version (MMAS-4) in statin treatment [41,42]. Self-reporting with different methods or instruments has been used in adherence trials using MI [20] and in many studies of adherence interventions in general [11]. For the combined adherence measure, patients will be regarded as nonadherent in the implementation phase if they score <6 points on the MMAS-8 [37,39]. However, to further investigate the relationship between different adherence measures and the outcome, we will tabulate the results from the MMAS-8, refill adherence, and LDL-C assessments and perform statistical analyses, using the 3 categories of high (8), medium (6 to 7.75), and low (<6) adherence in MMAS-8 [38].

Refill adherence will be assessed using the Swedish Prescribed Drug Register. Patients will be defined as nonpersistent if they have not purchased the drug at least once during the 12- to 16-month period after discharge. The 4-month period is based on the Swedish reimbursement system [43]. The proportion of patients who are persistent to dosage regimens for cholesterol-lowering drugs, aspirin, platelet aggregation inhibitors, beta-blocking agents, angiotensin-converting enzyme inhibitors, and angiotensin receptor blockers will be assessed using refill data compared with prescription data, as recorded in the EHR. For cholesterol-lowering drugs, a third adherence estimate will be used, the percentage of days covered adherence measure. A cutoff point of 80% has been set for the percentage of days covered measure [44]. This means that if a patient has collected medicines during the follow-up period, but has not collected enough to cover 80% of the doses prescribed in the EHR, the patient is considered either nonadherent during implementation or as having discontinued treatment.

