### Study Parameters and Data Collection

Baseline assessment data, including demographics, level of education, civil status, CHD presentation type, previous CHD history, comorbidities, smoking status, type of cardiovascular intervention, and prescribed medicines, were collected from the EHR by a member of the research staff before randomization. Further baseline data were obtained from questionnaires sent to the participants by mail after their physician visit at the cardiology clinic with instructions to return them within 10 days; these questionnaires covered medication adherence, beliefs about medicines, and health-related quality of life. Baseline data on lipid status and blood pressure were collected from the EHR. See Table 2 for a full list of the collected data and Figure 1 for an outline of study assessments.

To promote participant retention, control group patients receive a postal card stating the appreciation of the research team for their return of questionnaires at baseline and 10 months. Intervention group patients do not receive a card as they are instead summoned for a visit.

Lipid status and blood pressure are assessed 12-14 months after discharge. Patients who have had a myocardial infarction are followed-up at 12-14 months by the national quality register SEPHIA (Secondary prevention after Heart Intensive care Admission), and assessments of lipids and blood pressure are therefore recorded in the EHR. We use these data so that participants do not need an extra assessment because of the study. For noninfarction patients, the research team arranges for the assessment of lipids and blood pressure. All patients contacted by either SEPHIA or the research team receive a referral for a laboratory test and blood pressure measurement, which they can choose to do at the drop-in clinic at the hospital or at their primary care facility.

At 15 months postdischarge, participants complete all questionnaires for the outcomes assessment: Morisky 8-item adherence scale (MMAS-8), BMQ-S, EuroQoL 5 Dimensions 5 Levels, and HeartQoL questionnaire. A time of 15 months was chosen to relate the answers on the MMAS-8 to the pharmacy refill date 12-16 months after discharge. Data are collected from the Swedish Drug Prescription Register (adherence), the Health Care Register of Kalmar County (hospital admissions), and, for deceased participants, the registry of Causes of Death administered by the National Board of Health and Welfare.

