## Discussion

This protocol describes the methodology for a study assessing the effectiveness of an intervention involving extended follow-up of the pharmacological treatment of patients with CHD using MI and medication review. Our randomized controlled trial acknowledges that optimal prescribing and monitoring of medications as well as high patient adherence is a prerequisite for adequate secondary prevention.

The aim of the intervention is to improve secondary prevention of CHD, and the effectiveness will be measured by assessing patient adherence as well as intermediate biological outcomes such as relevant treatment outcomes, perceived quality of life, and number of hospital admissions. We use two complementary adherence measures: self-report and pharmacy refill for the cholesterol drugs, which are directly linked to the primary outcome: LDL-C.

The design of this adherence intervention is based on a theoretical framework and it is the first trial of an intervention that uses beliefs about medicines to individualize the intervention protocol. Many adherence interventions have failed to assess or find long-term effects. Because this intervention follows the patient throughout the year after hospitalization for CHD and targets all patients regardless of adherence, we hope that it can prevent patients from discontinuing their medicines in the long term. It has been shown that the greatest loss in adherence (persistence) is during the first year and that patients who are persistent at 2 years continue to be adherent [47].

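### In the exploratory adherence–LDL-C analysis, MMAS-8 and 12–16 month refill persistence are measured mainly after the LDL-C sample, so their association with goal achievement is blurred and partly reverse-ordered

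*Protocol article*

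**What the plan says.** Four statements in the protocol article fix the timing.

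- LDL-C (Study Parameters and Data Collection): "Lipid status and blood pressure are assessed 12-14 months after discharge". Table 2 places the lipid panel in its 12-month column.
- Self-report (same section): "At 15 months postdischarge, participants complete all questionnaires for the outcomes assessment", MMAS-8 among them. The reason given is "A time of 15 months was chosen to relate the answers on the MMAS-8 to the pharmacy refill date 12-16 months after discharge".
- Refill persistence (Secondary Outcomes, Patient Adherence): a patient is nonpersistent "if they have not purchased the drug at least once during the 12- to 16-month period after discharge".
- Days covered (same section): "For cholesterol-lowering drugs, a third adherence estimate will be used, the percentage of days covered adherence measure", with an 80% cutoff. Its period is described only as follow-up, with no start or end month given.

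The combined adherence measure for cholesterol-lowering drugs is built from self-report and refill persistence. Beyond the between-arm comparison, the same section plans to look at how the adherence measures relate to the outcome: "we will tabulate the results from the MMAS-8, refill adherence, and LDL-C assessments and perform statistical analyses", using three MMAS-8 categories.

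Strengths and Limitations says that lipids were kept at the 12-month follow-up for practical reasons, while adherence follow-up runs to 15 months. It does not discuss what this means for relating the two.

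**The concern.** MMAS-8 and the refill window are matched to each other, but neither is matched to the blood sample. An LDL-C value reflects the drug taken before it was drawn, and these two measures describe mainly what happened afterwards. This has two consequences.

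- **Misclassification.** A patient off the statin at a month-12 sample who buys again at month 14 is scored persistent with a high LDL-C. A patient at goal at month 12 who then stops and buys nothing more is scored nonpersistent with LDL-C at goal. Both kinds of error pull the association toward zero.
- **Reverse order.** LDL-C results are recorded in the health record, which hospital and primary care share. An above-goal result could prompt a restart, so adherence as scored may partly respond to the outcome that it is being related to.

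What is at stake is the interpretation of one exploratory analysis. A weak association could be taken as evidence that adherence matters little for LDL-C, or an observed one as evidence that adherence produced goal achievement. The timing of these two measures supports neither reading well.

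**Working it through.** The plan gives no figure to reproduce here, so the check is on the dates, followed by an illustration.

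**1. Order of measurement.** Let *t* be the month of the LDL-C sample, 12 to 14. The share of the refill window after the sample is (16 − t)/4, and the MMAS-8 lag is 15 − t.

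| t (months) | Refill window after sample | MMAS-8 lag (months) |
|---|---|---|
| 12 | 4/4 = 100% | 3 |
| 13 | 3/4 = 75% | 2 |
| 14 | 2/4 = 50% | 1 |

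No part of the refill window precedes month 12. These are shares of calendar time, not of patients misclassified: a patient who takes the drug throughout is scored correctly whenever the purchase falls.

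**2. Days covered.** The article does not give the exact window. Assume a start *s* of month 0 or 3 and an end *e* of month 12, 15 or 16. The share before the sample is (t − s)/(e − s), capped at 100%.

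- Lowest: s = 3, e = 16, t = 12 gives 9/13 = 69%.
- With s = 3, e = 15: 9/12 = 75% at t = 12 and 11/12 = 92% at t = 14.
- With e = 12: 100%.

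Under every one of these choices, most of the window precedes the sample.

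**3. Size of the attenuation (illustration).** All inputs are assumptions. Per 100 patients, 80 are on the drug at the sample with goal rate 0.55, and 20 are off it with goal rate 0.10. The true difference is 0.45. After the sample a fraction *r* of those off restart and a fraction *p* of those on stop, and they are scored by their later status:

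- goal rate if scored persistent = [80(1 − p)(0.55) + 20r(0.10)] / [80(1 − p) + 20r]
- goal rate if scored nonpersistent = [20(1 − r)(0.10) + 80p(0.55)] / [20(1 − r) + 80p]

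| r | p | Persistent | Nonpersistent | Difference | Attenuation |
|---|---|---|---|---|---|
| 1/3 | 0.05 | 42.47/82.67 = 0.514 | 3.53/17.33 = 0.204 | 0.310 | 31% |
| 0.10 | 0.03 | 42.88/79.6 = 0.539 | 3.12/20.4 = 0.153 | 0.386 | 14% |
| 0.05 | 0.02 | 43.22/79.4 = 0.544 | 2.78/20.6 = 0.135 | 0.409 | 9% |

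**4. Cross-check with stopping only.** The Introduction says that 20–30% of patients stop at some point. If that is treated as an annual rate with constant hazard (an assumption), 1.8% of those on treatment stop within 1 month at the lower rate and 8.5% within 3 months at the higher. With r = 0, the nonpersistent goal rate is 2.81/21.47 = 0.131 or 5.75/26.82 = 0.214. The difference is then 0.419 or 0.336, an attenuation of 7% or 25%, which is of similar size.

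**The case against.** The strongest reply is that the plan promises no more than an association. It sets out to examine how the adherence measures and LDL-C relate and states no mediation or causal aim. The trial's objectives are between-arm comparisons, which this timing does not touch. That stands, and it limits the point to an exploratory analysis.

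Second, a measure that mostly precedes the sample is already planned. Days covered for cholesterol-lowering drugs is a refill measure, and nothing excludes it from the refill adherence in "we will tabulate the results from the MMAS-8, refill adherence, and LDL-C assessments and perform statistical analyses". This also stands. Its exact start and end are details that an article can leave to the full protocol, so their absence is not held against the plan.

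Third, adherence at 12–16 months is a reasonable proxy for adherence shortly before the sample, and the 12-month lipid timing is openly explained as practical. Both are fair. But the proxy is imperfect, and the disclosure does not reach the adherence–LDL-C analysis.

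A reader might go further and infer that the analysis cannot show any link, or that a true effect acting through adherence could look absent. The documents do not support that: even the most pessimistic scenario above leaves a difference of 0.31.

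A reader might also take "self-report and pharmacy refill for the cholesterol drugs, which are directly linked to the primary outcome: LDL-C" as a claim that the measures are aligned in time with LDL-C. The phrase more naturally explains why the cholesterol drugs were chosen. Likewise, the criticism of earlier trials concerns their power to detect differences in adherence and clinical outcomes. It does not fault them for failing to relate the two within patients.

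**Conclusion.** The point holds in limited form. On the plan's own dates, all outcome MMAS-8 responses and 50–100% of the 12–16 month refill window follow the LDL-C sample. The combined adherence measure inherits this. The associations of these measures with LDL-C are likely attenuated and partly reverse-ordered, and should not be read as showing that adherence explains goal achievement.

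The order of measurement follows from the text. The size does not: the 9–31% range rests on assumed goal rates and on assumed stopping and restarting after the sample, and the upper end depends on one third of those off the drug restarting. That an LDL-C result changes later adherence is plausible but not documented.

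Days covered is less affected. The primary LDL-C comparison, the between-arm adherence comparisons and the sample size are unaffected. Severity is minor and confined to an exploratory analysis.

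**What to change.** For the adherence–LDL-C analysis only:

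- Derive cholesterol-lowering refill adherence in a window that ends on each patient's LDL-C sample date: days covered up to that date, and at least one purchase in the preceding 4 months. A sample at month 12 would use months 8–12, and one at month 14 would use months 10–14.
- Keep the 12–16 month persistence measure unchanged as the between-arm secondary outcome. This preserves comparability with the national Open Comparisons figure used in the sample size section.
- Label the tables of MMAS-8 and of 12–16 month persistence against LDL-C as associations in which adherence was measured mainly after the blood test. Self-report cannot be re-timed, because Table 2 schedules it only at baseline and 15 months.

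The cost is one additional derived variable and a few lines of analysis text. No new data collection should be needed: a 12–16 month purchase rule and a days-covered measure already require dated dispensings from the register, and the LDL-C results come with the health record data.

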##### Systolic Blood Pressure

We will also measure the proportion of patients with systolic blood pressure <140 mm Hg 12 months after discharge. As for LDL-C, this is part of the second follow-up in SEPHIA. Patients not included in the SEPHIA registry will be followed by the research team and asked to attend their primary care facility or the cardiology outpatient clinic for assessment, whichever is most convenient for them.

##### Quality of Life

Changes in quality of life will be measured with the HeartQoL [45] questionnaire. This questionnaire was developed for use in patients with ischemic heart disease; it measures both physical and emotional items. Mean changes between baseline and follow-up will be calculated for each group, as well as the proportion of patients with increased, maintained, or decreased quality of life. Our rationale for measuring this is that the items of HeartQoL would be affected partly if the treatment is better but possibly more by reducing side effects. It might be that increased treatment or adherence has a negative impact or that a more individual treatment leads to improved quality of life because of fewer side effects. However, there could also be negative consequences on the preventive effect for CHD. Although quality of life is challenging to evaluate, and multiple instruments can be used, there is reason to believe that this could be an important outcome in adherence interventions [46].

##### Secondary Care Use

Information about the patients’ unscheduled secondary care use will be collected from the health care register in the County of Kalmar. The number of emergency visits or hospitalizations due to cardiovascular disease and the time to first contact will be recorded for each group. Data will also be collected retrospectively for the 10-year period before the index date so that adjustments can be made as required.

## Results

A total of 417 patients were included in the study before recruitment stopped in December 2016, see Figure 2. Unmet inclusion criteria were later identified for 12 patients, standard follow-up was delayed by more than 3 months for 10 patients, 5 patients were excluded for other reasons, 1 was deceased, and 3 were missed in administration, which resulted in 386 patients being sent baseline questionnaires. By April 2017, all had been approached and given baseline questionnaires and 317 patients had answered the questionnaires; 69 patients have withdrawn their participation by failing to return their baseline questionnaires.

Baseline characteristics have been registered in our database for the 234 subjects with baseline data collected before September 2016; these are described in Table 3. The mean (SD) age of the subjects is 68 (10.3) years and 73.9% (173/234) are male. About 70% (161/234) of the participants have had a myocardial infarction or other acute event, and about 30% (66/234) of participants have an earlier history of CHD. Medicines prescribed at discharge to these subjects can be seen in Table 4.

